## 8.0 DOSE AND TREATMENT MODIFICATIONS

### 8.1 Ancillary Therapy, Concomitant Medications, and Supportive Care

All supportive therapy for optimal medical care will be given during the study period at the discretion of the treating physician(s) within the parameters of the protocol and documented on each site's source documents as concomitant medication.

*Herbal and Nutritional Supplement:* The concomitant use of herbal therapies is generally not recommended, as their pharmacokinetics, safety profiles, and potential drug-drug interactions are generally unknown. However, the use of general nutritional foundation supplements will be allowed including: calcium with vitamin D and/or minerals, Omega3s (fish oil), Vitamin B6, Vitamin B12, basic multivitamins, L-glutamine, or probiotics oral supplements will be

permitted either at or below the recommended dosing by a healthcare provider. Herbal-based multivitamins are not allowed.

**8.1.1 Patients should not receive any other treatment which would be considered**

treatment for the primary neoplasm or impact the primary endpoint. This includes any surgical intervention, radiotherapy, cryotherapy, systemic therapy, ablation, etc.

**8.1.2 Patients should receive full supportive care while on this study.** This includes blood product support, antibiotic treatment, and treatment of other newly diagnosed or concurrent medical conditions. All blood products and concomitant medications such as antidiarrheals, analgesics, and/or antiemetics received from the first day of study treatment administration until 30 days after the final dose will be recorded in the medical records.

**8.1.3 G-CSF**

- Use of growth factors during consolidative chemotherapy is permitted on this study, while use of growth factors during chemotherapy + XRT phase is prohibited. Do not administer G-CSF within 24 hours of chemotherapy. See Section 8.2 for treatment modifications/management. The use of growth factors should follow published guidelines of the American Society of Clinical Oncology Clinical Practice Guideline Update. J Clin Oncol 33: 3199-3212, 2015.
- Use of epoetin in this protocol is discouraged
- Choice of growth factor for neutropenia is at the investigator's discretion.
- If needed, pegfilgrastim and filgrastim are recommended; however, if required by institutional standards, GM-CSF may be administered as an alternative. Biosimilars are also permitted based on institutional practice.
- Loratadine (10 mg) or similar agents are permitted if pegfilgrastim is used.

**8.1.4 Management of nausea or vomiting**

Antiemetic therapy should be administered according to National Comprehensive Cancer Network (NCCN) (<https://www.nccn.org>) or American Society of Clinical Oncology (ASCO) clinical practice guidelines (Hesketh 2017). See Section 8.2 for dose modifications and delays.

**8.1.5 Management of Diarrhea**

Diarrhea is a commonly occurring toxicity with the therapies included in this protocol. Without appropriate treatment, diarrhea can be prolonged, severe, and lead to dehydration and other complications. (See [Appendix I](#) for clinical management of diarrhea.)

Inform patients that they may experience diarrhea while on chemotherapy and possibly for several weeks after chemotherapy has stopped.

Patients **must** be instructed to:

- have ready access to antidiarrheal agents (e.g., loperamide) starting on Day 1 of treatment.
- All patients must be instructed to begin taking loperamide at the earliest sign of poorly-formed or loose stools ( $\geq$  grade 1). Early intervention is important for patient safety. See Section 8.2 for dose modifications and delays.
- continue prophylactic therapy as directed

- promptly report diarrhea symptoms
- report constipation *before* taking any laxatives or stopping antidiarrheal medication.

Patients who have multiple loose bowel movements and any worsening of fatigue, nausea, vomiting, right upper quadrant abdominal pain or tenderness, fever, rash, or eosinophilia should be promptly evaluated for changes in liver function. (See [Appendix I](#) for sample patient instructions for diarrhea management.)

Aggressive supportive care should be provided for patients with grade 4 ANC and  $\geq$  grade 3 diarrhea until neutropenia and diarrhea resolve. See [Appendix I](#) for clinical management of diarrhea. Hospitalization for evaluation and management of grade 3 or grade 4 complicated diarrhea, as defined in [Appendix I](#), is strongly recommended.

Refer to the ASCO Recommended Guidelines for Treatment of Cancer Treatment-Induced Diarrhea for additional recommendations regarding diarrhea (Benson 2004).

### 8.1.6 Management of pharyngolaryngeal dysesthesias

Oxaliplatin may cause discomfort in the larynx or pharynx associated with the sensation of dyspnea, anxiety, and swallowing difficulty. Exposure to cold can exacerbate these symptoms.

Refer to Section 8.2 for dose modification instructions.

Do NOT use ice chips or other forms of oral cryotherapy to decrease stomatitis in conjunction with oxaliplatin.

Anxiolytics may be used at the physician's discretion.

### 8.1.7 Management of Irinotecan-related cholinergic syndrome (Experimental Arm)

- Lacrimation, rhinorrhea, miosis, diaphoresis, hot flashes, flushing, abdominal cramping, diarrhea, or other symptoms of early cholinergic syndrome may occur during or shortly after receiving irinotecan. Atropine, 0.25-1.0 mg IV or SC may be used to treat these symptoms or may be used prophylactically. Additional antidiarrheal measures may be used at the discretion of the investigator.
- Combination anticholinergic medications containing barbiturates or other agents (e.g., Donnatal®) should not be used because these may affect irinotecan metabolism. Anticholinergics should be used with caution in patients with potential contraindications (e.g., obstructive uropathy, glaucoma, tachycardia, etc.).
- Diarrhea developing more than 24 hours after the irinotecan dose should be managed with loperamide per protocol.

### 8.1.8 Hypersensitivity/infusion reactions

Treat hypersensitivity and infusion reactions to oxaliplatin per institutional standards.

### 8.1.9 Drug/drug interactions

- **Coumarin:** Altered coagulation parameters and/or bleeding, including death, have been reported in patients taking capecitabine concomitantly with coumarin-derivative anticoagulants such as warfarin and phenprocoumon. These events occurred within several days and up to several months after initiating capecitabine therapy and, in a few cases, within 1 month after stopping capecitabine. These events occurred in patients with and without liver metastases.

- **It is required that the INR be monitored carefully** (at least weekly) while the patient is receiving treatment with capecitabine and warfarin concurrently and for an additional 4 weeks following the patient's last capecitabine dose. Institutional standards for this drug combination should be followed closely. Subcutaneous heparin or fractionated heparin products are permitted.
- **Phenytoin:** Increased phenytoin levels have also been reported in patients taking capecitabine concurrently with phenytoin and, therefore, need to be monitored.
- Chronic concomitant treatment with strong inhibitors or inducers of CYP3A4 is not allowed on this study. Patients on strong CYP3A4 inhibitors or inducers must discontinue the drug for 14 days prior to registration on the study.

## 8.2 Dose Modifications

The CTCAE v5.0 must be used to grade the severity of AEs. Refer to [http://ctep.cancer.gov/protocolDevelopment/electronic\\_applications/ctc.htm](http://ctep.cancer.gov/protocolDevelopment/electronic_applications/ctc.htm).

Deviations from the recommended treatment modifications/management must be documented in the patient treatment record.

In the event of disease recurrence, second primary colorectal cancer, or diagnosis of an invasive second primary/secondary malignancy, study therapy will be discontinued; further therapy is at the investigator's discretion. Tests, exams, and assessments **are required** and patients will continue to be followed off treatment for vital status per protocol.

If, in the opinion of the investigator, a toxicity is considered to be due solely to one component of the study treatment (i.e., 5-FU, capecitabine, oxaliplatin, or irinotecan) and the dose of that component is held or modified in accordance with the guideline below, the other components may be administered per protocol guidelines.

If several toxicities with different grades of severity occur at the same time, the dose modifications should be according to the highest grade observed.

Any chemotherapy doses that have been reduced may not be escalated.

**For any concomitant conditions apparent at baseline, the dose modifications will apply according to the corresponding shift in toxicity grade, if the investigator feels it is appropriate.** For example, if a patient has Grade 1 asthenia at baseline that increases to Grade 2 during treatment, this will be considered a shift of one grade and treated as Grade 1 toxicity for dose-modification purposes only.

**For specific questions or concerns regarding this section, please contact [name] [[contact]](mailto:[contact]) and/or [name] [mailto:[name]\\[contact]](mailto:[contact]).**  
In the event of treatment-related AEs during consolidation chemotherapy that requires treatment hold for  $\geq 30$  days from the date of the planned cycle, consolidation chemotherapy should be discontinued. If consolidation chemotherapy is discontinued because of delay, patients the subject should be referred for presurgical restaging as detailed in the study calendar in section 5.0

In the event of non-treatment related AEs that result in dose delays of 30-60 days and have resolved to grade  $\leq$  grade 1 by 60 days from the date of the planned cycle, patients may continue with consolidation chemotherapy if deemed in their best interest by the treating oncologist.

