### 8.2.1 Dose Levels

*Chemotherapy dose modifications for patients are detailed in Tables 8.2.1.2 and 8.2.1.3. Dose modifications are based on the dose level changes outlined in Table 8.2.1.1. Additionally, the following mFOLFOX6 dose modification instructions must be followed:*

All doses must be based on the AE requiring the greatest modification.

Any chemotherapy doses that have been reduced may not be escalated.

- If  $\geq$  grade 2 toxicity occurs **during the 46-48 hour infusion of 5-FU**, discontinue the infusion, and refer to Table 8.2.1.2 for dose modifications for the next cycle of mFOLFOX6.
- The leucovorin dose remains 400 mg/m^2 regardless of changes in the 5-FU and oxaliplatin doses. If 5-FU is held, leucovorin should also be held.
- If oxaliplatin is discontinued, treatment should continue with 5-FU and leucovorin.

Table 8.2.1.1. mFOLFOX6 dose levels

|                                                                                                                                                                              | Dose Level 0
Starting Dose
(mg/m  ) | Dose Level -1
(mg/m  ) | Dose Level -2
(mg/m  ) | Dose Level -3 |
|------------------------------------------------------------------------------------------------------------------------------------------------------------------------------|---------------------------------------------------------------------|----------------------------------------------|----------------------------------------------|----------------------|
| Oxaliplatin                                                                                                                                                           | 85                                                                  | 65                                           | 50                                           | Discontinue          |
| Leucovorin*                                                                                                                                                           | 400                                                                 | 400                                          | 400                                          | Discontinue          |

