|-------------------------------------------------------------------------------------------------------------------------------------------------------------------------------------------------------------------------------------------------------------------------------------------------------------------------------------------------------------------------------------------------------------------------------------------------------------------------------------------------------------------------------------------------------------------------------------------------------------------------------|----------------------------------------------------------------------------------------------------------------------------------------|---------------------------------------------------------------------------------------------------------------------------|
| 
 
• All dose modifications for mFOLFOX6 are based on the dose level changes on Table 8.2.1.1.
 
• Dose modifications must be based on AEs that occurred during the cycle (column 2) and AEs present on the scheduled Day 1 of Cycles 2-12 (column 3).
 
• Refer to footnote a for management of anemia.
 
• Modifications in dose levels apply to 5-fluorouracil and oxaliplatin unless otherwise indicated; leucovorin doses remain unchanged.
 
• Dose modifications must be based on the AE requiring the greatest modification.
 
 |                                                                                                                                        |                                                                                                                           |

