| Grade 3                                                                               | Maintain dose

Consider use of growth factors to avoid delay with subsequent cycles.     | Consider use of growth factors to avoid delay with subsequent cycles.

Hold until <math>\geq 1500/\text{mm}^3</math>. If recovery takes:

1 wk – maintain dose;
$\geq 2$ wks – ↓ one dose level |
| Grade 4                                                                               | ↓ one dose level.

Consider use of growth factors to avoid delay with subsequent cycles. | Consider use of growth factors to avoid delay with subsequent cycles.

Hold until <math>\geq 1500/\text{mm}^3</math>.
↓ one dose level.                                                               |
| Platelet count decreased:
Grade 2                                                  | Maintain dose                                                                                         | Hold until <math>\geq 75,000/\text{mm}^3</math>.
If recovery takes:
1-3 wks – maintain dose
$\geq 3$ wks – ↓ one dose level                                                                           |
| Grade 3,4                                                                                           | ↓ one dose level                                                                                      | Hold until <math>\geq 75,000/\text{mm}^3</math>. ↓ one dose level                                                                                                                                                     |
| GI:
Diarrhea ( despite optimal antidiarrheal management )
Grade 2 | Maintain dose                                                                                         | ↓ only 5-FU one dose level                                                                                                                                                                                                   |

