| Grade 2                                                                    | Maintain dose                                                                | ↓ oxaliplatin one dose level                                                                                                                               |
| Grade 3                                                                    | ↓ 5-FU and oxaliplatin one dose level                                        | Hold until bilirubin returns to the baseline grade and AST and alk phos have returned to ≤ grade 1, then:
↓ 5-FU and oxaliplatin two dose levels |
| Grade 4                                                                    | Discontinue                                                                  | Discontinue                                                                                                                                                |
| Febrile neutropenia:                                         | Consider use of growth factors to avoid delay with subsequent cycles. | Consider use of growth factors to avoid delay with subsequent cycles.                                                                               |
| Grade 3                                                                    | ↓ one dose level                                                             | ↓ one dose level                                                                                                                                           |
| Grade 4                                                                    | ↓ one dose level                                                             | Discontinue                                                                                                                                                |
| Infection:                                                   |                                                                              |                                                                                                                                                            |

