### 8.2.2 Treatment management for patients receiving CAPOX

Capecitabine dose modifications for patients treated with CAPOX are detailed in Table 8.2.2.2. See Tables 8.2.1.2 and 8.2.1.3 for oxaliplatin-specific toxicities. Dose modifications are based on the dose level changes outlined in Table 8.2.2.1.

Additionally, the following dose modification instructions must be followed:

All dose modifications should be based on the adverse event requiring the greatest dose modification.

If capecitabine is held or discontinued, oxaliplatin continues per protocol unless otherwise contraindicated.

Capecitabine and oxaliplatin doses that have been reduced may not be escalated.

Table 8.2.2.1. CAPOX (capecitabine per day in two divided doses) dose levels

|                     | Dose Level 0
Starting Dose
(mg/m  /d) | Dose Level -1
(mg/m  /d) | Dose Level -2
(mg/m  /d) | Dose Level -3 |
|---------------------|-----------------------------------------------------------------------|------------------------------------------------|------------------------------------------------|----------------------|
| Oxaliplatin  | 130                                                                   | 100                                            | 85                                             | Discontinue          |
| Capecitabine | 2000                                                                  | 1500                                           | 1000                                           | Discontinue          |

Table 8.2.2.2. Treatment management for capecitabine (See Tables 8.2.1.2 and 8.2.1.3 for oxaliplatin-specific toxicities.)

|                                                                                                                                                                                                                                                                                                                                                                                                                                                             |                                    |

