| Grades 2 (ANC 1000-1500/mm  )                           | Reduce irinotecan one dose level
Consider use of growth factors to avoid delay with subsequent cycles.                                     | Consider use of growth factors to avoid delay with subsequent cycles.

Hold until <math>\geq 1500/\text{mm}^3</math>. If recovery takes: 1-2 wks – maintain dose <math>\geq 2</math> wks - ↓ one dose level                                                                                |
| Grade 3                                                             | Reduce irinotecan one dose level. Maintain dose level of other drugs
Consider use of growth factors to avoid delay with subsequent cycles. | Reduce irinotecan one dose level.
Consider use of growth factors to avoid delay with subsequent cycles.

Hold until $\geq 1500/\text{mm}^3$ .

For other drugs:

1 wk – maintain dose or ↓ one dose level at discretion of treating oncologist;
$\geq 2$ wks – ↓ one dose level |
| Grade 4                                                             | Reduce irinotecan one dose level. Maintain dose level of other drugs
Consider use of growth factors to avoid delay with subsequent cycles. | Reduce irinotecan two dose levels; reduce doses of other drugs by 1 dose level.
Consider use of growth factors to avoid delay with subsequent cycles.

Hold until $\geq 1500/\text{mm}^3$ .                                                                                                    |
| Platelet count decreased:                             |                                                                                                                                                      |                                                                                                                                                                                                                                                                                                                |

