| Diarrhea ( despite optimal antidiarrheal management ) |                                                                                                                                                      |                                                                                                                                                                                                                                                                                                                |
| Grade 2                                                             | ↓ irinotecan one dose level                                                                                                                          | ↓ 5-FU and irinotecan one dose level                                                                                                                                                                                                                                                                           |
| Grade 3                                                             | ↓ 5-FU, oxaliplatin, and irinotecan one dose level                                                                                                   | ↓ 5-FU, oxaliplatin, and irinotecan one dose level                                                                                                                                                                                                                                                             |

|                       |                                                                                         |                                                                                         |
|-----------------------|-----------------------------------------------------------------------------------------|-----------------------------------------------------------------------------------------|
| Grade 4               | ↓ 5-FU and oxaliplatin one dose level, irinotecan two dose levels                | Discontinue                                                                             |
| Mucositis oral |                                                                                         |                                                                                         |

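### Section 8.2 doses concurrent toxicities by the highest grade, the regimen sections by the greatest modification; no precedence is stated, and some combinations get different doses

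*Combined protocol and SAP*

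**What the plan says.** Section 8.2 (Dose Modifications) sets general rules before the regimen sections. For concurrent toxicities it says: "If several toxicities with different grades of severity occur at the same time, the dose modifications should be according to the highest grade observed". It makes no exception for regimen-specific text.

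The regimen sections that follow state a different rule:

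- 8.2.1 (mFOLFOX6): "All doses must be based on the AE requiring the greatest modification". The instructions at the head of Table 8.2.1.2 repeat it: "Dose modifications must be based on the AE requiring the greatest modification".
- 8.2.2 (CAPOX): "All dose modifications should be based on the adverse event requiring the greatest dose modification".
- 8.2.3 (mFOLFIRINOX): the same sentence as in 8.2.1, repeated at the head of Table 8.2.3.2.

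In all three sections the rule comes under a lead-in that presents it as an additional and mandatory instruction. Section 8.2.4 (chemoradiation) states no rule of its own for concurrent toxicities. For capecitabine and 5-FU toxicity it refers to Table 8.2.2.2 and names Section 8.2.2 as its location.

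**The concern.** One criterion looks at the CTCAE grade, the other at the action the table assigns. They are equivalent only if a higher grade always carries at least as large an action, whatever the type of event. The tables are not built that way: hematologic events often carry a smaller change than non-hematologic events one grade lower.

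This is an operative dosing and stopping rule. Where the criteria diverge, a site that obeys Section 8.2 literally departs from the regimen section, and the reverse also holds. At stake are the next-cycle dose and, in one type of case, whether chemotherapy continues at all.

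**Working it through.** The documents give no figure to reproduce. The check is to take pairs of events with different grades, read the dose from the row of the higher-grade event (Section 8.2), then read it from the row of the event with the greater change (regimen rule).

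**Inputs.** Dose levels 0, -1 and -2 in mg/m²:

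- Table 8.2.1.1 (mFOLFOX6): oxaliplatin 85, 65, 50; 5-FU bolus 400, 320, 270; 5-FU infusion 2400, 1920, 1600.
- Table 8.2.3.1 (mFOLFIRINOX): oxaliplatin 85, 65, 50; 5-FU infusion 2400, 1920, 1600; irinotecan 150, 135, 120.
- Table 8.2.2.1 (CAPOX): capecitabine 2000, 1500, 1000 per day.

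Every example starts at level 0. In each, one event's row is at least as large for every drug, so no drug-by-drug mixture of rows is needed.

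**Example 1. mFOLFIRINOX, both events resolved before the next cycle (Table 8.2.3.2).** Grade 4 neutropenia: "Reduce irinotecan one dose level. Maintain dose level of other drugs". Grade 3 diarrhea lowers "5-FU, oxaliplatin, and irinotecan one dose level".

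| Drug | Highest grade | Greatest modification | Difference |
|---|---|---|---|
| 5-FU | 2400 | 1920 | 480/2400 = 20.0% |
| Oxaliplatin | 85 | 65 | 20/85 = 23.5% |
| Irinotecan | 135 | 135 | none |

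**Example 2. mFOLFOX6, both events in the delay column (Table 8.2.1.2).** Grade 4 neutropenia lowers both drugs "one dose level". A grade 3 hepatic event lowers "5-FU and oxaliplatin two dose levels".

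| Drug | Highest grade | Greatest modification | Difference |
|---|---|---|---|
| Oxaliplatin | 65 | 50 | 15/65 = 23.1% |
| 5-FU bolus | 320 | 270 | 50/320 = 15.6% |
| 5-FU infusion | 1920 | 1600 | 320/1920 = 16.7% |

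The same pair in mFOLFIRINOX: grade 4 neutropenia with delay takes irinotecan down two levels and the other drugs one. The grade 3 hepatic row takes everything down two. 5-FU is 1920 or 1600, oxaliplatin 65 or 50, and irinotecan 120 under both.

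**Example 3. mFOLFOX6 or mFOLFIRINOX, delay column, grade 4 neutropenia or thrombocytopenia with grade 3 vomiting despite antiemetics.** The hematologic row reduces: mFOLFOX6 to oxaliplatin 65, bolus 320 and infusion 1920; mFOLFIRINOX to oxaliplatin 65, 5-FU 1920 and irinotecan 120. The vomiting row, which covers grades 3 and 4 together, discontinues. One rule continues chemotherapy and the other stops it.

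**Secondary example. CAPOX (Table 8.2.2.2).** Grade 4 neutropenia that recovers in 1 week keeps the capecitabine dose. A first grade 3 event in the continued part of the table lowers it one level: 2000 or 1500 mg/m²/day, a difference of 500/2000 = 25%. The heading of that second block is not visible in the text available. Its footnote suggests other clinically significant events, so this example carries less weight.

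**How widely the rules agree.** The main event rows were coded for two columns, and all pairs of different events with different grades were compared. Under this coding the rules differ in 9 of 154 pairs for mFOLFIRINOX (resolved column) and in 12 of 154 for mFOLFOX6 (delay column). They agree in 145/154 = 94% and 142/154 = 92%. The counts take the larger change drug by drug, assume short hematologic recovery, and leave out the neuropathy and other-event rows. They show that conflict is the exception. They are not frequencies among patients.

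**The case against.** The strongest reply is that the protocol signals which rule governs. Section 8.2 says *should*; the regimen rules come under a lead-in that says *must*. They are more specific, and for mFOLFOX6 and mFOLFIRINOX they are printed again at the head of the table where the dose is looked up. The CAPOX sentence itself says *should*, but under the same mandatory lead-in. To go wrong, a site would have to let a general sentence override the table header and, in Example 3, an explicit instruction to discontinue. This stands as evidence of intent and limits the practical risk. It is still an inference: the lead-in adds to Section 8.2 without replacing it, and Section 8.2 yields to nothing.

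It is also fair that the doses above are less fixed than they look. Section 8.2 lets the investigator attribute a toxicity to one component and continue the others, and asks that deviations be documented. That discretion applies under either rule and does not settle which rule is the starting point.

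A reader might infer that the highest-grade sentence is the only rule for chemoradiation. The documents do not support that. The pointer in 8.2.4 names Section 8.2.2 along with its table, and 8.2.2 carries the greatest-modification rule, although under a CAPOX heading.

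A reader might also infer an effect on the trial's comparisons, because stopping for toxicity before 8 cycles counts in the early-off-treatment rate of Section 13.5.1. The documents give no frequency for these combinations, so no such effect can be shown.

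**Conclusion.** The inconsistency is real and limited. Two current rules use different criteria, none is ranked above the other, and most combinations give the same dose under both. In the examples the Section 8.2 sentence gives the higher dose: in Examples 1 and 2, for the drugs that differ, the regimen rule lies about 16% to 24% lower. In Example 3 it continues chemotherapy that the regimen table stops. The regimen rule is probably what the sponsor intends.

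This rests on starting doses at level 0, on both events being read from the same column of the table, and on no use of the single-component discretion. It does not rest on the CAPOX example. The point should be corrected because it concerns a safety-relevant instruction. It does not put an endpoint, an analysis or a monitoring boundary in doubt.

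**What to change.** In Section 8.2, replace the highest-grade sentence with one saying that, when several toxicities coincide, the rule already in the tables applies: "Dose modifications must be based on the AE requiring the greatest modification". That aligns the general text with 8.2.1, 8.2.2 and 8.2.3.

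The same sentence would make chemoradiation consistent with the section to which 8.2.4 refers. No separate chemoradiation rule is needed unless the sponsor wants a different one, in which case one sentence in 8.2.4 would state it.

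The cost is one sentence in the next amendment, with no added procedures.
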